## Consent

As described below, participants provide informed consent before engaging in study activities. In keeping with the anonymous nature of the “Seek and Test” study phase, verbal informed consent will be obtained. Participants entering the “Treat and Retain” study phase will provide signed informed consent.

### Screening for eligibility for the Seek and Test Phase

Verbal consent for a brief screening interview is obtained. Study staff will review the informed consent form for screening with potential participants and obtain their verbal informed consent for a brief, computerized screening interview to determine eligibility. Study staff will use a handheld or laptop computer to document the participant’s informed consent and then conduct the screening interview, which covers the eligibility criteria noted above. Individuals are given a copy of the screening informed consent form for their records. No names or identifying information will be collected from study participants; only unique identifiers will be used. Participants are compensated $15 for their time for this screening interview. Additionally, funds for local round-trip public transportation for all in-person encounters (assessments, sessions, navigation) are provided.

### Enrollment in the Seek and Test phase

Individuals who meet the eligibility criteria and are interested in participating in the Seek and Test phase will provide verbal informed consent to enroll into this phase, documented using a handheld/laptop computer. The consent form explains that this phase of the study is anonymous, and reviews study activities including a computerized baseline interview; an HIV pre-test counseling session; blood draw for HIV testing; use of blood samples for clinical lab tests (viral load, CD4), if found to be HIV infected; and a post-test counseling session to receive test results. Compensation levels are explained at this time. Individuals are given a copy of the informed consent form for the Seek & Test phase, and told that if they are found HIV-infected, the project will provide support to them as they adjust to their diagnosis. Participants are informed that, with their consent, if they are found to be HIV-positive, blood specimens will be tested for HIV viral load levels for research purposes without names, and that unused blood will be discarded. If their HIV test results are negative, all of their remaining blood specimens will be discarded. Individuals must agree to the baseline interview and counseling session to enroll in the study, which take place on the same day, but can decline the other components and continue in the study.

### Baseline interview

Participants then engage in a brief baseline interview (< 30 min) conducted in audio computer-assisted self-interviewing (ACASI) format. The assessment battery is comprised of a set of measures used in the National Institute on Drug Abuse (NIDA) funded STTR projects for vulnerable populations, assessing domains such as socio-demographic characteristics, HIV testing history, substance use frequency, substance use problems, and sexual partners [6, 49]. Participants are compensated $20 for their time for this assessment.

### Counseling intervention session and HIV testing

Individuals then complete a private one-on-one intervention/ counseling session led by a study staff member, lasting approximately 30–40 min, guided by the MI approach. The underlying goal of the first session is to engage participants into the study, build trust and relationships, and foster motivation to engage in study activities. The session consists of a series of brief exercises. First, participants are introduced to the study. The study rationale is described, and respect for participants’ choices and decisions throughout is emphasized. This includes the core message that if the participant tests positive for HIV, the study staff will help them get the high quality care they need, and if the participant tests HIV-negative, the study will provide them with referrals to help them stay that way. Second, the distinction between the anonymous Seek & Test study phase and the confidential Treat and Retain phase is briefly described, again with an emphasis on participants’ choices and autonomy. Third, HIV pre-test counseling is provided, consisting of a review of elements either required or recommended by the CDC and local Department of Health, such as a review of the nature of HIV and HIV transmission and risk reduction, review of the benefits of HIV testing and early treatment, explanation that HIV testing is voluntary, explanation of anonymous and confidential testing, and a review of confidentiality and discrimination protections and partner notification services. Next, participants receive a brief training on how to recruit peers for the study, and are encouraged to do so. This includes: who to recruit, how and when to approach peers, and how to refer peers to the project using a coded recruitment coupon. Then, a highly trained, experienced phlebotomist draws a blood specimen, which is sent to a laboratory for HIV testing, and a handout describing next steps in the study is reviewed, namely, the participant is asked to return to the project in approximately 7–14 days to collect compensation for peer recruitment (if any) and meet with the interventionist for post-test counseling and test results.

The blood specimen is transported using packaging mandated in the Federal Code of Regulations, CDC 42 CRF Part 72 and tested with the 4^th^ generation Alere assay (HIV-1/O/2 Antigen/Antibody Preliminary Test with Cascade Reflex to Supplementary Testing). The 4^th^ generation HIV test allows diagnosis of the earlier, acute phase (recent) of HIV infection, prior to the emergence of antibodies, effectively reducing the period after initial infection and before the detection of infection based on formation of detectable antibodies. The local Department of Health recommends the use of the 4^th^ generation HIV testing algorithm [50]. All work with human fluids is conducted at Biosafety Level 2. At this time, blood specimens are processed and stored for future HIV viral load testing if the participant tests positive for HIV. (It is not possible to store specimens for CD4 testing, so a second blood draw is conducted as appropriate in the second session.) Participants are compensated $15 for their time for this session, and $25 for the blood draw for HIV and viral load testing. They can complete the session and decline the blood draw and HIV testing.

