### Our research team’s studies of STTR approaches

We recently published a protocol describing a study of two approaches for uncovering individuals with undiagnosed HIV infection [27]. One is a “Seek and Test” study using venue-based sampling (VBS) as its recruitment method. This approach provides confidential HIV counseling and testing in a single session in randomly selected public venues. The second approach is an STTR study using respondent-driven sampling (RDS) to enroll participants, followed by two intervention sessions (for engagement and training in how to recruit peers in the first session, and confidential HIV counseling and testing using a rapid HIV test provided in the second session), followed by care navigation to link those found HIV infected to health care in a timely fashion [27]. (The activities that make up the care navigation approach are described below.) RDS is a sampling methodology for studying subpopulations that are hard to define, reach, and/or engage. RDS is network-based method , similar to traditional snowball sampling, but with the goal of minimizing biases typically associated with those traditional methods [26, 28]. In RDS, a modest number of individuals are recruited directly by project staff (called “initial seeds”), and then trained to recruit a small number of their peers into the study. These peers then enter the study and peer recruitment continues until the sample size goals are met [26, 29]. The RDS method has four essential elements: tracking of recruitment chains; rationing of recruitment (usually 2–5 peers each); information on personal networks must be gathered (network size, recruitment refusals); and recruiters and recruits must have a pre-existing relationship [21]. We refer to this former study as VBS and the latter study as RDS-CTTN (“Confidential Two-session Testing with Navigation”). These two STTR studies are located in central Brooklyn, a location within New York City with high rates of poverty and highly prevalent HIV infection among heterosexuals, where African American/Black and Latino populations predominate [27]. In the present protocol we describe an innovative third STTR approach being evaluated in the same high-risk area in central Brooklyn, focused on the same vulnerable population of HHR. In contrast to the RDS-CTTN and VBS approaches which are providing confidential HIV testing, this “hybrid” approach begins with anonymous HIV testing in its “Seek and Test” phase, and then delivers intervention components to engage those found to be HIV infected in to a confidential “Treat and Retain” phase in order to link them to HIV care in a timely fashion, using care navigation.

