### Outcomes

The primary outcome of the Seek and Test phase is the relative yield (that is, proportion of newly identified HIV infections) of the RDS-ASTN intervention. We will assess the proportion of those newly diagnosed that engages in activities of the Treat and Retain phase (i.e., the feasibility of switching from an anonymous to a confidential phase). The primary endpoints for the Treat and Retain phase are the proportion linked to HIV primary care within three months (i.e., attending a care appointment and receiving CD4 and viral load tests) and time to the HIV care appointment. We will assess the acceptability and safety of the intervention components, as well as their cost-effectiveness. Because we examine many of these same endpoints in the other two components of the STTR study (VBS, RDS-CTTN), we can compare findings across the three STTR strategies.

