### Hypotheses

The study will explore the following hypotheses: compared with VBS and RDS-CTTN, and controlling for potential differences on key socio-demographic characteristics across the samples, RDS-ASTN participants will have less HIV testing experience. Further, controlling for potential differences on key socio-demographic characteristics across the samples, RDS-ASTN will yield substantially higher rates of previously undiagnosed HIV compared with VBS and modestly higher rates compared to RDS-CTTN, although the RDS-ASTN intervention is less labor intensive than RDS-CTTN. This is because the brief and anonymous nature of the RDS-ASTN intervention may appeal to highly vulnerable individuals with multiple barriers to HIV testing. Further, we hypothesize that most participants (> 70 %) found to be HIV-infected in the RDS-ASTN intervention will engage in the Treat and Retain phase of the study, grounded in the efficacy of the MI approach combined with compensation based on behavioral economics principles to foster engagement. Last, we hypothesize that most participants in the Treat and Retain part (> 70 %), all of whom will be HIV infected, will be linked to care within 3 months, based on past studies of care navigation with similar populations [42, 43].

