### Analysis plan

First, we will compare the yield of RDS-ASTN with the two other STTR strategies we described in a separate protocol, RDS-CTTN and VBS [27], with respect to newly diagnosed HIV infection. We will examine differences in demographic characteristics between VBS, RDS-CTTN and RDS-ASTN participants and adjust for these when comparing STTR approaches. Logistic regression will be used to compare the three STTR strategies on yield of newly diagnosed HIV infection. Covariates will include prior HIV testing.

Second, we will explore the feasibility of engaging RDS-ASTN participants who test HIV-positive into a confidential Treat and Retain study phase. Key indicators of feasibility will include the percentage of participants with HIV infection who accept the transition from the anonymous testing phase to the confidential Treat and Retain phase; and rates of engagement in Treat and Retain phase study activities. We also will explore the efficacy of the Treat and Retain components in terms of time to an HIV clinic appointment among newly identified HIV-infected HHR. We will describe the occurrence and timing of a first HIV clinic appointment and whether viral load and CD4 results were obtained. Cox proportional hazards regression will be used to compare STTR strategies (RDS-CTTN and RDS-ASTN) on the occurrence and timing of first HIV clinic appointment.

Third, we will project the clinical impact, costs, and cost-effectiveness of RDS-ASTN for identifying HHR, and linking them to and retaining them in HIV-related medical care. Incremental cost-effectiveness ratios (ICER) will be presented in terms of costs per HIV infection prevented and used to compare STTR strategies. We will estimate the costs and effectiveness outcomes for ICERs with projections from a mathematical model of HIV infections prevented, based on reductions in HIV risk behavior [58, 59] and viral load suppression associated with treatment [60, 61]. For outcomes not directly observed in participants recruited by RDS-ASTN, we will assume these are the same as for the RDS-CTTN intervention group; that is, an RDS-ASTN participant linked to care and retained for three months has the same probabilities of ART initiation and viral load suppression as an RDS-CTTN participant. The time horizon for our analysis is lifetime.

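### The yield comparison of RDS-ASTN with RDS-CTTN may be confounded by assay: a 4th-generation laboratory test on one side, an unspecified rapid test on the other

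*Protocol article*

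**What the plan says.** The Outcomes section defines the primary Seek and Test outcome as "the relative yield (that is, proportion of newly identified HIV infections) of the RDS-ASTN intervention". The Analysis plan states: "Logistic regression will be used to compare the three STTR strategies on yield of newly diagnosed HIV infection". It adjusts for demographic differences between the samples and for prior HIV testing.

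The tests are described in two places:

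- **RDS-ASTN** (Counseling intervention session and HIV testing): drawn blood is sent to a laboratory for a 4th-generation antigen/antibody assay with reflex supplementary testing. The stated property is: "The 4^th^ generation HIV test allows diagnosis of the earlier, acute phase (recent) of HIV infection, prior to the emergence of antibodies".
- **RDS-CTTN and VBS** (Our research team's studies of STTR approaches): RDS-CTTN provides "confidential HIV counseling and testing using a rapid HIV test provided in the second session". For VBS the text says "This approach provides confidential HIV counseling and testing in a single session in randomly selected public venues", with no assay named.

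The Hypotheses section expects RDS-ASTN to show "modestly higher rates compared to RDS-CTTN", and explains its expected advantage this way: "This is because the brief and anonymous nature of the RDS-ASTN intervention may appeal to highly vulnerable individuals with multiple barriers to HIV testing". The Limitations section comments on comparability of compensation across the three studies but does not mention the tests.

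**The concern.** Yield counts what a test detects. If the RDS-ASTN assay finds infections that the RDS-CTTN test would miss, the two studies could have the same undiagnosed prevalence and still report different yields. All RDS-ASTN participants who are tested have one assay and, as described, all RDS-CTTN participants have another. A logistic model with participant characteristics therefore has no information with which to separate assay from strategy.

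If the rapid test's window is narrower, the bias runs one way, towards RDS-ASTN, on the primary outcome. It would do so in the contrast where the article expects the smaller difference. Acute infections found only because of the assay could then be read as support for the anonymous, brief format.

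**Working it through.** **Inputs from the article**
- RDS-ASTN: 500 enrolled, 40 newly diagnosed; 40/500 = 8% (Study population and sampling considerations).
- Detectable odds ratio against RDS-CTTN: 1.71, with 80% power and α = .05 (Power analysis).
- Over 55,000 new infections a year, and 14% of 1.2 million people with HIV undiagnosed (Background).

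The OR of 1.71 can be neither reproduced nor refuted, because the RDS-CTTN sample size and base rate are not given. It serves here only as a yardstick. With 8% in RDS-ASTN it implies comparator odds of (0.08/0.92)/1.71 = 0.0509, a rate of 4.84%.

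**Formula.** Let f be the share of RDS-ASTN new diagnoses that the rapid test would have missed. With a true rate of 8% in both studies:

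spurious OR = [0.08/0.92] / [0.08(1−f) / (1 − 0.08(1−f))]

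The article does not give f, so two ranges are shown.

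**Range A: f from the Background figures.** Undiagnosed pool: 0.14 × 1,200,000 = 168,000. In steady state, the share of that pool lying within an extra detection window of w days is about 55,000 × (w/365) / 168,000. The value of w is an assumption.

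| w (days) | f | Cases of 40 | Spurious OR | Share of ln 1.71 |
|---|---|---|---|---|
| 7 | 0.6% | 0.25 | 1.007 | 1.3% |
| 14 | 1.3% | 0.5 | 1.014 | 2.6% |
| 30 | 2.7% | 1.1 | 1.030 | 5.5% |

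**Range B: f assumed directly.**

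| f | Cases of 40 | Spurious OR | Share of ln 1.71 | An observed 1.71 becomes |
|---|---|---|---|---|
| 5% | 2 | 1.06 | 10% | 1.62 |
| 10% | 4 | 1.12 | 21% | 1.53 |
| 15% | 6 | 1.19 | 33% | 1.43 |

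The last column removes the antibody-negative cases from RDS-ASTN. At f = 10%, for example, 36/500 = 7.2% against 4.84% gives 1.53.

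**How the ranges relate.** Under the Range A formula, f = 5% needs w = 0.05 × 168,000 × 365 / 55,000 ≈ 56 days, and f = 15% needs about 167 days. Range B is therefore an upper scenario.

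**Limits.** If f = 0, the OR is 1.00. For the assay alone to produce 1.71, f would have to be 1 − 0.0484/0.08 = 39.5%.

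**The case against.** **The rapid test is not characterised.** The article gives no generation, window or confirmatory algorithm for it and refers to a separately published protocol. A reader might infer that part of any yield difference must come from the assay, or that RDS-ASTN would show a higher yield even at equal prevalence. The article does not support that: a rapid test that detects the same infections would leave no bias. This stands, and it makes the point conditional.

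**The effect is likely small.** On the Background figures it is about one of 40 cases or fewer. The article also says that this population tests less often and is diagnosed later than other risk groups, which lowers the acute share further. This stands. It rules out presenting the 10 to 33% shares of the log odds ratio as the expected size.

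**The assay is part of the strategy.** The planned comparison is between whole packages, and the local health department recommends the 4th-generation algorithm. That is a fair reason to keep the all-infections comparison. It does not support crediting the difference to anonymity and brevity, because the article justifies the assay separately from both.

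**Restricting the count could itself bias.** If the rapid test also detects antigen, removing antibody-negative cases from RDS-ASTN alone would undercount it. This stands, and the restricted count should not be the main analysis.

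**The full protocol or analysis plan may cover it.** A sensitivity analysis may be specified there, and its absence from an article is not the point. The point is that the two tests, the comparison between them and the explanation for the expected difference are all stated here and do not fit together without a qualification.

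**Conclusion.** The point holds as a possible, one-directional confounding of the RDS-ASTN versus RDS-CTTN yield comparison. The article describes different tests, credits the RDS-ASTN assay with detection before antibodies appear, and plans an adjustment that cannot address the difference.

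The size is unknown and probably small. The spurious OR is about 1.01 to 1.03 for an assumed extra window of 7 to 30 days, assuming steady state, the national figures in the Background and a comparator test that misses every infection in that window. It would be about 1.06 to 1.19 if 5 to 15% of new diagnoses were antibody-negative, a share for which the article gives no source. It is nil if the tests detect the same infections. Within these ranges the assay could not by itself produce an OR of 1.71.

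A reader might extend the point to VBS because testing there takes place in one session in public venues. The article names no VBS assay, so nothing can be concluded.

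**What to change.** 1. Keep the comparison of all newly diagnosed infections as planned.
2. State the type and detection window of the RDS-CTTN rapid test, and name the VBS assay.
3. Report RDS-ASTN antibody-negative (acute) infections separately, where the supplementary results identify them. The article names reflex supplementary testing but not its components, so confirm that the recorded results allow this.
4. If the RDS-CTTN test has a narrower window, prespecify a sensitivity analysis that repeats the logistic yield model with only the infections that both tests could detect.
5. Add the assay difference to the Limitations section, and do not attribute any excess of acute infections to anonymity or brevity.

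The cost is slightly more analysis and a slightly lower RDS-ASTN count in the sensitivity analysis. No additional recruitment, visits or testing are needed.

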### Building motivation to return for test results

The study includes a number of techniques to boost the proportion of participants who return for test results, which are necessary given that participants cannot be contacted or reminded about future activities. Drawing on work by Volpp and colleagues [51] that shows people are motivated by the experience of past rewards and the prospect of future rewards, participants in the first intervention session will enter a lottery with a good probability of winning a modest prize, namely, a 1 in 5 chance of winning $25, and a high probability of winning the smaller prize; that is, a 4 in 5 chance of winning $10 (a "high-odds, low-dollar" lottery) [51]. In the second session, participants will have a chance to participate in a "low-odds, high-dollar" lottery, with a 1 in 38 chance of winning a $50 prize, with the remainder receiving a low-dollar prize ($15). Second, participants are asked to address an appointment reminder card to themselves at the conclusion of the first intervention session, and place it themselves in a locked box, the contents of which are not visible to staff. Study staff will empty the cards from the lock box into a mailbox at the end of each day, without seeing any names or addresses. These retention methods will be explained in the consent form of the Seek and Test part. The study does not involve deception in any phase; all procedures are transparent.

### Peer recruitment period

After the intervention session, participants then enter the “peer recruitment period” of approximately 7–14 days during which they have the opportunity to recruit 2–6 peers to the study (depending on study recruitment patterns) using coded recruitment coupons that link the recruiter’s unique identification number to the recruit. When 3 or more coupons are distributed, at least one of the coupons is designated for females only, to boost the proportion of women in the study. Participants follow a recruitment script that instructs them to recruit individuals aged 18 – 60 years old; who they know by name or face, and who live in the larger HRA. Peers will be screened for eligibility, as described above. Recruiters receive $5 for each peer who presents for screening, plus a bonus of $10 for each eligible peer, for a total of $15 per eligible peer.

